## Abstract

**Background:**

Polycystic ovary syndrome (PCOS) affects between 8 and 18% of women and is the leading cause of female anovulatory infertility. Unfortunately, common treatments for women trying to conceive can be ineffective as well as disruptive or harmful to patients’ quality of life. Despite evidence that women with PCOS have expressed the need for alternative fertility treatments, lifestyle interventions incorporating a nutritional plan with supplementation, increased physical activity, and techniques for stress management have not been combined as a program and studied in this population. Literature suggests that each of these individual components can positively influence reproductive hormones and metabolic health.

**Methods/design:**

This is a randomized controlled trial which will include 240 women diagnosed with PCOS, according to the Rotterdam criteria, who are trying to conceive. Participants will be randomized to either a comprehensive lifestyle intervention program or prescribed an oral fertility medication, letrozole. These two groups will be further randomized to consume either myo-inositol or a placebo. Participants will be between the ages of 18 and 37 years. Exclusion criteria include women who have already begun fertility treatment, who are currently using myo-inositol or have taken it within the past 3 months, or who are being treated for, or have a history of, an eating disorder. The primary outcome will be the ovulation rate, the secondary outcome will be conception. Other outcomes include miscarriage rates, validated rating measures of overall quality of life (including social, relational, mind/body and emotional sub-categories) and mental health scores (depression, anxiety, and stress).

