## Background

Polycystic ovary syndrome (PCOS) is a heterogenous endocrine syndrome characterized by chronic anovulation and hyperandrogenism (clinical or biochemical) according to the original 1990 NIH criteria. The 2003 Rotterdam criteria added the presence of polycystic ovarian morphology on ultrasound which resulted in four distinct PCOS phenotypes. PCOS is also associated with obesity, insulin resistance, metabolic syndrome, reduced quality of life, increased anxiety and higher rates of depression [1]. Between 70 and 80% of women with PCOS have difficulty conceiving due to oligo- or anovulation. Despite ovulation rates of 75–80% achieved with the use of ovulation-induction agents and a conception rate per cycle of 22% (comparable to that of a healthy women trying to conceive naturally in their first year), some women with PCOS remain unresponsive [2, 3]. In contrast, evidence suggests that lifestyle (diet, activity and stress management) influences ovulation and the effectiveness of fertility treatments [4–6].

While lifestyle intervention is recommended as first-line management for women with PCOS and obesity, 45% of women with PCOS reported that they have never received information on lifestyle management and only 61–76% of reproductive endocrinology and infertility obstetric gynecologists (REI-ObGyn) and 46–61% of obstetric gynecologists (ObGyn) recommended lifestyle modifications to patients for fertility or non-fertility problems [7, 8]. Even with efforts to improve dietary and exercise habits, women with PCOS often have difficulty managing their weight. In addition, 62% of women with PCOS reported never receiving information about emotional support or counseling [7]. It appears that attention to general physical and psychological health is inconsistent at the clinical level yet recognized as an important factor in the effective management of women receiving the life-altering diagnosis of PCOS and/or infertility [9, 10].

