In addition to a low-glycemic diet, physical activity, and stress reduction, a diet supplemented with myo-inositol may provide further hormonal homeostasis and improve metabolic functioning [20]. Myo-inositol is one of nine stereoisomers of inositol and sometimes considered a member of the B complex vitamin family, albeit humans can synthesize this isomer from glucose. It acts as a second messenger in insulin signaling pathways. Several studies have shown that insulin resistance with its compensatory hyperinsulinemia play a pivotal role in both the metabolic and ovarian hormone dysfunction observed in PCOS women. There is evidence that women with PCOS and insulin resistance could be deficient in myo-inositol which would impact glucose metabolism. In addition, myo-inositol levels in follicular fluid are lower in PCOS women with hyperinsulinemia compared to healthy women [21, 22]. An earlier study described that higher levels of myo-inositol in follicular fluid correlated with oocyte quality and maturity [23]. When supplemented with myo-inositol, women with PCOS have experienced reduced serum insulin, testosterone, and increased rates of ovulation [24, 25]. Myo-inositol has also been shown to improve oocyte number and quality [26].

We hypothesize that implementing a comprehensive program of lifestyle changes in women with PCOS will help restore ovulation by weight loss, reduce serum androgen levels and increase sensitivity to insulin. A lifestyle change program could also ameliorate hirsutism over time. Such changes should improve overall psychological well-being and quality of life. Finally, we expect that distinct phenotypes of PCOS will respond differently to lifestyle intervention. Such information will allow us to better determine which phenotypes are best served using our comprehensive approach, and to identify more specifically those factors affecting outcomes.

The objectives of this study are: to determine whether the comprehensive lifestyle intervention described is effective in restoring ovulation and compare this to letrozole; to determine whether the addition of myo-inositol improves ovulation rates, insulin resistance, metabolic parameters; and finally to evaluate differences in the responses for each of four main PCOS phenotype sub-groups.

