## Statistical methods

The participants’ biochemical and hormonal profiles, physical attributes (body mass index (BMI), hirsutism), ovulatory response, pregnancy status, scores for depression, anxiety, stress and quality of life will be assessed for statistical normality. Each main effect will be compared by analysis of variance (ANOVA) or its non-parametric equivalents. The primary comparison will be between GLC and letrozole. The observed effects of myo-inositol alone are small in clinical experience and there are no reported interactions between myo-inositol and ovulation-induction medications or lifestyle change in the literature. Hence, our power calculations (see below) have been based on the two main effects acting independently. However, our factorial design will provide an opportunity to explore potential interactions (acknowledging the sample size required would change in the presence of interactions) [30, 31]. Categorical data will be compared by chi-square statistics. Differences in dietary intake and dietary composition over time will be compared by ANOVA or its non-parametric equivalent with time as the repetitive measure. Regression analysis will also be performed to determine the individual impacts of diet, activity, and mindfulness on ovulation. In addition, membership in the four PCOS sub-groups will be further explored as a potential predictor for ovulation rates in regression analysis after adjusting for BMI and age.

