### Sample size and power calculations

Assuming no interactions between the two main effects as discussed earlier, the target sample size will be 240 participants (120 participants in the GLC group and 120 participants on oral medication). This is based on: a power calculation using a 5% significance level, 80% power comparing two proportions, and current knowledge of the average ovulation rates of lifestyle interventions and letrozole, our primary comparison. We explored a number of combinations of the ovulation rates from letrozole and lifestyle interventions and chose the most conservative estimate to ensure that our sample size was adequate, i.e., 91 in each group. By enrolling 120 participants in each group, we have allowed for a drop-out rate of 32%. Table 1 describes the lowest and highest reported ovulation rates for letrozole and lifestyle interventions, the sample size required in each scenario comparing the two proportions, and the three highest sample sizes required from our calculations, accounting for the length of lifestyle intervention and the start dose of letrozole.

**Table 1 Tab1:** Sample size calculation based on previous literature

Range of reported ovulation rates	Letrozole ovulation rate	Lifestyle ovulation rate	Total sample size needed
Lowest	62%^a^	38%^b^	130
Highest	86%^c^	67%^d^	150
Median	70%	50%	182

^a^Legro et al. [29]

^b^Palomba et al. [36]

^c^Zeinalzadeh et al. [37]

^d^Karimzadeh and Javedani [38]

When calculating the sample size necessary to assess the effect of myo-inositol on ovulation rates, we reviewed the few published studies available acknowledging that these studies all had small sample size. One randomized controlled trial reported an ovulation rate of 70% when myo-inositol was given to women with PCOS versus a 21% ovulation rate in controls [24]. Similarly, another randomized controlled trial reported an ovulation rate of 65% using myo-inositol in PCOS [32]. Using these rates in a comparison of two proportions, a total sample size of 26 is needed, and easily covered by our original calculation above.

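### Rotterdam entry admits women without anovulation, so a yes/no ovulation outcome cannot show restoration in all of them, and the stated 80% power is at risk

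*Protocol article*

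**What the plan says.** **Eligibility.** The abstract (Methods/design) describes the sample as "240 women diagnosed with PCOS, according to the Rotterdam criteria, who are trying to conceive". The exclusions it lists concern earlier fertility treatment, myo-inositol use and eating disorders. None concerns ovulation at baseline.

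**Phenotypes.** The Background names chronic anovulation and hyperandrogenism as the older criteria and says that the Rotterdam revision "added the presence of polycystic ovarian morphology on ultrasound which resulted in four distinct PCOS phenotypes". The objectives at the end of the Background include comparing responses across all four. Under Statistical methods, "membership in the four PCOS sub-groups will be further explored as a potential predictor for ovulation rates", with adjustment for BMI and age.

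**Question and outcome.** The first objective is to find out whether the lifestyle programme is "effective in restoring ovulation and compare this to letrozole". Under Outcomes, the primary outcome is ovulation as a yes/no category, together with a count from 0 to 3, over a period that allows three possible cycles.

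**Sample size.** The section on sample size uses "a power calculation using a 5% significance level, 80% power comparing two proportions". The row of Table 1 that drives the number is "Median 70% 50% 182", and the authors "chose the most conservative estimate to ensure that our sample size was adequate, i.e., 91 in each group". They enrol 120 per arm to cover drop-out. The section states no expected phenotype mix and makes no allowance for women who ovulate at entry.

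**The concern.** Any two or more of three features (anovulation, hyperandrogenism, polycystic morphology) give four combinations: all three features, or one of three pairs. One pair is hyperandrogenism with polycystic morphology and no anovulation. By asking for all four phenotypes, the protocol admits that group deliberately.

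Three things follow.

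- **Objective against outcome.** Ovulation cannot be restored in a woman who has not lost it, yet she can count as a success in either arm.
- **Dilution.** If such women ovulate at similar rates in both arms, the GLC–letrozole difference shrinks in proportion to their share, and a real difference is easier to miss.
- **Phenotype regression.** The phenotype without anovulation will tend to predict ovulation because of how it is defined, whatever the treatment. Adjusting for BMI and age does not remove that.

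**Working it through.** **1. Reproduce the plan's figure.** Inputs from the sample size section: two proportions, 5% level (two-sided fits the table), 80% power. With unpooled variance and no continuity correction:

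n per arm = (1.960 + 0.842)² × [p₁(1−p₁) + p₂(1−p₂)] / (p₁−p₂)²

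For 70% versus 50%: 7.85 × (0.21 + 0.25) / 0.04 = 90.3, rounded up to 91, so 182 in total. The other two rows of Table 1 (130 and 150) also reproduce exactly. Power at 91 per arm is 80.3%.

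**2. Inputs that the article does not give.**

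- *Ovulatory share f.* The nearest statement is "Between 70 and 80% of women with PCOS have difficulty conceiving due to oligo- or anovulation". Its complement, 20–30%, is only a loose proxy for a fertility-clinic sample, so f is shown from 5% to 30%.
- *Ovulation rate in these women.* Taken as 95% in both arms.
- *Table 1 rates.* Taken first as rates in oligo- or anovulatory women. Step 5 drops this.
- *Balance.* The share and retention are taken as equal in the two arms.

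**3. All randomised women.** Each arm's rate is (1−f) × the Table 1 rate + f × 0.95, so the difference is 20 × (1−f) points. At f = 20%:

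- letrozole: 0.8 × 0.70 + 0.2 × 0.95 = 75%
- GLC: 0.8 × 0.50 + 0.2 × 0.95 = 59%
- at 91 per arm, z = 0.16 / √[(0.1875 + 0.2419)/91] = 2.33, and power = Φ(2.33 − 1.96) = 64%

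**4. Restricted to oligo- or anovulatory women.** The rates stay at 70% and 50%, with n(1−f) per arm. At f = 20% and 91 evaluable, n = 72.8, z = 0.20 / √(0.46/72.8) = 2.52, and power = 71%.

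| f | Rates, all women | Power, all women, 91 / 120 per arm | Power, restricted, 91 / 120 evaluable before restriction |
|---|---|---|---|
| 0% | 70% v 50% | 80% / 90% | same |
| 5% | 71.3% v 52.3% | 77% / 87% | 78% / 88% |
| 10% | 72.5% v 54.5% | 73% / 84% | 76% / 87% |
| 20% | 75% v 59% | 64% / 76% | 71% / 82% |
| 30% | 77.5% v 63.5% | 55% / 67% | 65% / 77% |

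Restriction gains about 3 points at f = 10% and 6 to 10 points at 20–30%. If all 120 per arm are evaluable, the unrestricted comparison keeps 80% power up to a share of about 14–15%, depending on whether the variance is pooled. At f = 20%, lowering the assumed rate in ovulatory women from 95% to 80% changes unrestricted power only to 63% / 75%.

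**5. If the Table 1 rates already mix phenotypes.** Then 70% and 50% contain the dilution, and 80% power at 91 per arm stands. At f = 20% the implied rates in oligo- or anovulatory women are (0.70 − 0.19)/0.8 = 63.75% and (0.50 − 0.19)/0.8 = 38.75%, a difference of 25 points. Restricting to 72.8 per arm gives about 88% power. Restriction therefore gains power under either reading.

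**The case against.** **A reader might infer that the trial fails to deliver 80% power, or that ovulatory women are known to sit near the ceiling in both arms.** The article supports neither as a fact. It gives no ovulatory share, no ovulation rate for that group, and no indication of whether the Table 1 studies excluded ovulatory women. The 20–30% range comes from a statement about all women with PCOS, while this sample comes from a fertility centre, where the share could be well below 20%. This stands, and it is why the power loss is stated conditionally.

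**The 70% versus 50% row is the most demanding one.** With f = 20% and 120 per arm, the other two rows of Table 1 keep about 85–87% power. This also stands, but the plan itself chose the demanding row to fix its number.

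**The restricted analysis changes the target population and does not by itself recover 80%.** The effect in all Rotterdam-defined women who want to conceive is a legitimate target. It is not what the stated objective of restoring ovulation describes, however, and the wider analysis can be kept as support. That restriction alone falls short at 91 evaluable is correct.

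**Phenotype is not ignored, and a count of ovulations is also recorded.** Both are true. Neither changes the yes/no comparison on which the sample size rests, and the planned regression does not separate baseline ovulation from treatment response.

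**A reader might infer that the plan would claim GLC equals letrozole if the rates came out alike.** It does not. It sizes a test of difference and sets no equivalence margin.

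**The full eligibility list may be longer than the article's.** That is possible, but a requirement for anovulation would remove one of the four phenotypes that the objectives ask for.

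**Conclusion.** The point holds in conditional form. The mismatch between objective, population and primary outcome follows from the article's own text and does not depend on the size of the ovulatory group. So does the problem with reading phenotype as a predictor of ovulation.

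The effect on power is a risk, not an established shortfall. It rests on an assumed share, an assumed 95% rate in both arms, and Table 1 rates that describe oligo- or anovulatory women. Under those assumptions any share much above zero takes power below 80% at the planned 91 evaluable per arm. With full retention of 120 per arm, power falls below 80% only once the share passes about 14–15%. If the Table 1 rates are already mixed, the stated power is not reduced, but the unrestricted comparison is still the less sensitive one.

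**What to change.** - Leave enrolment and the four phenotypes as they are.
- Define the primary GLC–letrozole comparison in women classified as oligo- or anovulatory before randomisation. Because the status is fixed beforehand, the comparison remains randomised.
- Report all randomised women as a supporting analysis adjusted for baseline ovulatory status.
- Present the phenotype analysis as the treatment effect within each phenotype, not as phenotype predicting ovulation.
- In the sample size section, give the expected phenotype mix, say which population the Table 1 rates describe, and restate power accordingly.

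**Cost.** Changes of wording only, and no extra participants. Ovulatory status is one of the Rotterdam features and so is needed for the diagnosis; the article does not say when phenotype is assigned, so the text should fix that it is recorded before randomisation. The price is a smaller primary analysis set and, probably, a less favourable power statement. At 91 evaluable per arm with unmixed rates, restriction still leaves 71% at a 20% share and 65% at 30%, so the restated power must accompany it. The Trial status section says recruitment has not begun, so the change can be made before any data exist.

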**Discussion:**

This trial will determine the effectiveness of a structured lifestyle-based comprehensive intervention program for women with PCOS experiencing infertility. In addition, it will determine whether supplementing with myo-inositol provides any further benefit. The objective of this study is to assess a possible non-pharmacological solution to ovulatory dysfunction in these patients and perhaps improve other associated features of PCOS.

**Trial registration:**

ClinicalTrials.gov, ID: NCT02630485. Registered on 15 December 2015.

**Electronic supplementary material:**

The online version of this article (10.1186/s13063-018-3009-5) contains supplementary material, which is available to authorized users.

## Background

Polycystic ovary syndrome (PCOS) is a heterogenous endocrine syndrome characterized by chronic anovulation and hyperandrogenism (clinical or biochemical) according to the original 1990 NIH criteria. The 2003 Rotterdam criteria added the presence of polycystic ovarian morphology on ultrasound which resulted in four distinct PCOS phenotypes. PCOS is also associated with obesity, insulin resistance, metabolic syndrome, reduced quality of life, increased anxiety and higher rates of depression [1]. Between 70 and 80% of women with PCOS have difficulty conceiving due to oligo- or anovulation. Despite ovulation rates of 75–80% achieved with the use of ovulation-induction agents and a conception rate per cycle of 22% (comparable to that of a healthy women trying to conceive naturally in their first year), some women with PCOS remain unresponsive [2, 3]. In contrast, evidence suggests that lifestyle (diet, activity and stress management) influences ovulation and the effectiveness of fertility treatments [4–6].

While lifestyle intervention is recommended as first-line management for women with PCOS and obesity, 45% of women with PCOS reported that they have never received information on lifestyle management and only 61–76% of reproductive endocrinology and infertility obstetric gynecologists (REI-ObGyn) and 46–61% of obstetric gynecologists (ObGyn) recommended lifestyle modifications to patients for fertility or non-fertility problems [7, 8]. Even with efforts to improve dietary and exercise habits, women with PCOS often have difficulty managing their weight. In addition, 62% of women with PCOS reported never receiving information about emotional support or counseling [7]. It appears that attention to general physical and psychological health is inconsistent at the clinical level yet recognized as an important factor in the effective management of women receiving the life-altering diagnosis of PCOS and/or infertility [9, 10].

A survey of 657 women with PCOS found that 99% of participants would prefer to use alternative methods of treatment than those usually prescribed by their physicians such as clomiphene or oral contraceptives [11]. More recently a literature review by Arentz et al*.*, reported that 70% of women with PCOS use a variety of complementary and alternative medicines, such as vitamin, mineral and herbal supplements. While the most common reason given was to “treat PCOS,” other reasons included “to treat infertility,” “to improve general well-being,” and “to reduce depression” [12].

There have been no studies to date evaluating the reproductive outcomes of a comprehensive, three-component, intervention program incorporating structured nutritional and physical activity combined with techniques for stress management in women with PCOS trying to conceive [13]. The literature shows that women with PCOS can significantly benefit from lifestyle changes, specifically, eating a low-glycemic diet, incorporating nutritional supplements, increasing their activity level, and managing stress [14–17]. However, prior lifestyle intervention studies have limitations including high drop-out rates, lack of defining specific PCOS phenotypes, and small cohort sizes. In addition, most studies have focused on only one lifestyle-related change, such as diet, as opposed to a more synergistic approach wherein diet, exercise, and stress reduction are combined. In addition, the implementation of a mind/body program to help reduce stress which could potentially increase ovulation and conception has yet to be studied in a PCOS cohort. Cognitive behavioural therapy has been implemented in infertile populations for over 30 years [18]. These programs teach a variety of coping skills such as learning relaxation techniques, stress management, and provide group support. The relaxation response is a powerful tool already proven effective in stress-related diseases such as cancer, cardiovascular disease, and mental disorders. Since women with PCOS have a higher prevalence of mental health conditions, inducing the relaxation response through mindfulness training could prove an effective stress management strategy for our study cohort [19].

In addition to a low-glycemic diet, physical activity, and stress reduction, a diet supplemented with myo-inositol may provide further hormonal homeostasis and improve metabolic functioning [20]. Myo-inositol is one of nine stereoisomers of inositol and sometimes considered a member of the B complex vitamin family, albeit humans can synthesize this isomer from glucose. It acts as a second messenger in insulin signaling pathways. Several studies have shown that insulin resistance with its compensatory hyperinsulinemia play a pivotal role in both the metabolic and ovarian hormone dysfunction observed in PCOS women. There is evidence that women with PCOS and insulin resistance could be deficient in myo-inositol which would impact glucose metabolism. In addition, myo-inositol levels in follicular fluid are lower in PCOS women with hyperinsulinemia compared to healthy women [21, 22]. An earlier study described that higher levels of myo-inositol in follicular fluid correlated with oocyte quality and maturity [23]. When supplemented with myo-inositol, women with PCOS have experienced reduced serum insulin, testosterone, and increased rates of ovulation [24, 25]. Myo-inositol has also been shown to improve oocyte number and quality [26].

We hypothesize that implementing a comprehensive program of lifestyle changes in women with PCOS will help restore ovulation by weight loss, reduce serum androgen levels and increase sensitivity to insulin. A lifestyle change program could also ameliorate hirsutism over time. Such changes should improve overall psychological well-being and quality of life. Finally, we expect that distinct phenotypes of PCOS will respond differently to lifestyle intervention. Such information will allow us to better determine which phenotypes are best served using our comprehensive approach, and to identify more specifically those factors affecting outcomes.

The objectives of this study are: to determine whether the comprehensive lifestyle intervention described is effective in restoring ovulation and compare this to letrozole; to determine whether the addition of myo-inositol improves ovulation rates, insulin resistance, metabolic parameters; and finally to evaluate differences in the responses for each of four main PCOS phenotype sub-groups.

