## Methods/design

### Overall study design

Women diagnosed with PCOS will be recruited at the Grace Fertility and Reproductive Medicine Centre in Vancouver, Canada. This study follows a factorial design (Fig. 1). Participants will be randomized with a 1:1 allocation into two groups: the first group participating in a comprehensive lifestyle intervention program provided by our clinic (“Graceful Lifestyle Changes” (GLC) program) while the second group will be prescribed letrozole to induce ovulation, with the standard physician counseling (Fig. 2). Within each group, participants will be further randomized with a 1:1 allocation to either receive oral myo-inositol or a placebo. Block randomization will be performed at both stages using a computer-generated random numbers table and the software program REDCap. All clinicians, research scientists and participants involved in the study will be blinded to block sizes and allocation of myo-inositol/placebo. A researcher not involved in the study will be responsible for the randomization procedures. A data monitoring committee will not be necessary given the known safety of the proposed interventions. The SPIRIT 2013 Checklist for trial protocols has been included (see Additional file 1).

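### The objective of showing that the lifestyle programme restores ovulation is not one this design can meet unless the programme beats letrozole

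*Protocol article*

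**What the plan says.** The Background section of the protocol article gives the first objective in two parts: "to determine whether the comprehensive lifestyle intervention described is effective in restoring ovulation and compare this to letrozole". The Discussion paragraph of the abstract states the first part without qualification: "This trial will determine the effectiveness of a structured lifestyle-based comprehensive intervention program for women with PCOS experiencing infertility".

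Under Overall study design, the first randomisation is to GLC or to an active drug: "while the second group will be prescribed letrozole to induce ovulation, with the standard physician counseling". The second randomisation concerns the supplement only: "Within each group, participants will be further randomized with a 1:1 allocation to either receive oral myo-inositol or a placebo". The only placebo in the trial is therefore the one for myo-inositol, and all four factorial cells receive GLC or letrozole.

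Statistical methods fixes the contrast and the test: "The primary comparison will be between GLC and letrozole" and "Categorical data will be compared by chi-square statistics". The sample size rests on "a power calculation using a 5% significance level, 80% power comparing two proportions". Table 1 lists three pairs of ovulation rates, and the authors "chose the most conservative estimate to ensure that our sample size was adequate, i.e., 91 in each group". Enrolment is set at 120 per group. The article states no non-inferiority or equivalence margin.

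**The concern.** The first part of the objective is about the effect of GLC itself: do women ovulate because of the programme? That needs something to compare GLC with other than an active ovulation-inducing drug. The article describes neither an untreated group nor an external rate against which the GLC arm will be judged. It enrols by Rotterdam diagnosis and says itself that this definition covers four phenotypes, and that 70–80% of women with PCOS, not all, have difficulty conceiving because of oligo- or anovulation. Some women may ovulate during the 12 weeks without help, so the ovulation rate in the GLC arm alone cannot be credited to GLC.

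What is at stake is the sentence the investigators may write at the end. If letrozole wins, the trial has not shown whether GLC works. If the difference is non-significant, it is easy to conclude that GLC works, or works as well as the drug, although the test does not support either statement.

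**Working it through.** **Inputs.** From Table 1: letrozole vs lifestyle 62% vs 38%, 86% vs 67%, 70% vs 50%, with totals 130, 150 and 182. From the sample size section: 5% significance, 80% power, 91 per group planned, 120 per group enrolled. The 70% vs 60% and 70% vs 70% cases below are my assumptions; the article does not give them.

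**Step 1: reproduce Table 1.** Two-sided 5%, 80% power, unpooled variance: n = [p1(1−p1) + p2(1−p2)] × (1.960 + 0.842)² / (p1−p2)², with (1.960 + 0.842)² ≈ 7.849.

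- 62 vs 38: 0.4712 × 7.849 / 0.0576 = 64.2, so 65 per group, total 130.
- 86 vs 67: 0.3415 × 7.849 / 0.0361 = 74.3, so 75 per group, total 150.
- 70 vs 50: 0.4600 × 7.849 / 0.0400 = 90.3, so 91 per group, total 182.

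All three match. The article does not state sidedness, but a one-sided calculation with pooled variance gives 106, 122 and 148, so the table is a two-sided test of difference.

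**Step 2: what the trial is powered to find.** With the usual pooled-variance test, power = Φ{(|p1−p2| − 1.96·se0)/se1}, where se0 uses the mean of the two rates and se1 the separate rates.

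| Letrozole vs GLC | Power, 91 per group | Power, 120 per group |
|---|---|---|
| 62 vs 38 | 91% | 96% |
| 86 vs 67 | 86% | 94% |
| 70 vs 50 | 79% | 89% |

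In each row this is power to show that letrozole is better. Under these rates the chance of a significant result favouring GLC, with 120 per group, is below 1 in 1,000,000.

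**Step 3: what each possible result says about restoring ovulation.**

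- *GLC significantly better.* This supports effectiveness, provided letrozole does not itself leave women ovulating less than no treatment would. At 85% vs 70% with 120 per group: se0 = √(2 × 0.775 × 0.225/120) = 0.0539, se1 = √((0.21 + 0.1275)/120) = 0.0530, power = Φ{(0.15 − 0.1057)/0.0530} ≈ 80%.
- *Letrozole significantly better.* This answers the comparison but not the restoration question. Observed rates of 70% and 50% with 120 per group give GLC minus letrozole = −20 points, 95% interval −32 to −8. A 50% rate might be far above what these women would have reached untreated, or no higher. The one control rate in the article, 21%, comes from a cited myo-inositol trial and is not offered as a reference for GLC.
- *Not significant.* This shows neither restoration nor parity with letrozole (Step 4).

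**Step 4: how weak a non-significant result is (assumed rates).** At true rates of 70% vs 60%:

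- 91 per group: se0 = √(2 × 0.65 × 0.35/91) = 0.0707, se1 = √(0.45/91) = 0.0703; power = Φ{(0.10 − 0.1386)/0.0703} = 0.292; non-significant 71% of the time.
- 120 per group: se0 = 0.0616, se1 = 0.0612; power = Φ{(0.10 − 0.1207)/0.0612} = 0.368; non-significant 63% of the time.

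At equal rates of 70%, the 95% half-width is 1.96 × √(2 × 0.21/n) = 13.3 points (n = 91) or 11.6 points (n = 120).

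**The case against.** The objective also asks for a comparison with letrozole. The primary comparison is exactly that, and the randomised design answers it whichever way it falls. A clear letrozole win is useful information. This stands, and that half of the objective needs no repair.

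A reader might go further and infer that no result could support effectiveness. That is too strong: the test is two-sided, and a significant advantage over an active drug would support it. Such a result is remote under the tabulated rates, but the design does not exclude it. A reader might also infer that letrozole is ahead in every scenario considered. The article says several combinations were explored and shows only three, so only the tabulated ones are known.

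A reader might infer that the trial sets out to claim equivalence and therefore lacks a margin. The article never claims equivalence or non-inferiority; it speaks of a possible non-pharmacological solution and a successful programme. The missing margin is not an error.

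It can also be said that the effect measure and the reading of a null result are normally left to the analysis plan, and that baseline ovulatory status may be in the full protocol or the schedule figure. Both are fair, and I do not rely on their absence. A baseline measure would help describe the women, but without a concurrent untreated group it would not separate a GLC effect from natural variation. The objective, the comparator and the basis of the sample size are all stated in this article, and the mismatch is between them.

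Finally, 70% vs 60% is not a planning rate. For the deficits of 19 to 24 points that the article does plan for, a null result would be uncommon: 4% to 11% with 120 per group.

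**Conclusion.** The concern holds for the effectiveness half of the objective and for the abstract's conclusion. As designed, the trial estimates how GLC differs from letrozole. It can establish that GLC is effective only by GLC being significantly better, which has 80% power at about 85% vs 70% with 120 per group and is practically excluded under the tabulated rates. The result it is powered to find, letrozole ahead by 19 to 24 points, does not address restoration. A non-significant result does not either, and it is weak evidence of parity: 63% to 71% likely under an assumed true 10-point deficit, with an interval of about ±12 to ±13 points if both rates are 70%.

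The conclusion rests on the arms and contrast as described in the article. The sizes in the last sentence rest on assumed rates and on 91 or 120 evaluable women per group.

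**What to change.** Restate the first objective, and the matching sentence in the abstract's Discussion paragraph, as estimating the difference in ovulation between GLC and letrozole. Remove the statement that the trial will determine effectiveness or restoration. Name the risk difference with its 95% confidence interval as the primary result. Add one sentence saying that a non-significant difference will not be read as equal efficacy or as evidence that GLC restores ovulation.

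The cost is a narrower claim. No arm, patient or test changes, and the article's Trial status section says recruitment has not begun.

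A non-inferiority margin is not required, because the protocol does not claim non-inferiority. Adding one would not be free: at equal rates of 70% with 120 per group, power = Φ(margin/se − 1.96) with se = √(2 × 0.21/120) = 0.0592, which gives 39% for an assumed 10-point margin and 72% for 15 points.
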